### Ethics

This study is conducted in accordance with the principles of the Declaration of Helsinki and 'good clinical practice' guidelines. The medical ethical committee of the Academic Medical Centre Amsterdam has approved the study protocol (MEC number 08/183 # 08.17.1104). Prior to randomization, written informed consent will be obtained from all patients.

### Data-analysis

Since the main outcome of this study is the neoplasia recurrence rate, i.e. proportion of patients with recurrent disease, the Chi-square test will be used to compare the intervention groups (TEM versus EMR). Since the event of recurrence, and not time to recurrence, is the most important indicator for treatment failure, Kaplan Meier methods will not be used. The complication and mortality rates will be compared in the same manner. The number of days not spent in hospital as additional primary outcome measure will be compared by the Wilcoxon rank sum test.

Differences between the intervention groups in continuous outcome measures (e.g. Wexner incontinence scale, quality of life questionnaires) will be tested by the student's t-test or Wilcoxon rank sum test, where appropriate.

All analyses will be carried out primarily on an intention-to-treat basis.

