**Methods/design:**

Multicenter randomized trial among 15 hospitals in the Netherlands. Patients with a rectal adenoma ≥ 3 cm, located between 1–15 cm ab ano, will be randomized to a TEM- or EMR-treatment strategy. For TEM, patients will be treated under general anesthesia, adenomas will be dissected en-bloc by a full-thickness excision, and patients will be admitted to the hospital. For EMR, no or conscious sedation is used, lesions will be resected through the submucosal plane in a piecemeal fashion, and patients will be discharged from the hospital. Residual adenoma that is visible during the first surveillance endoscopy at 3 months will be removed endoscopically in both treatment strategies and is considered as part of the primary treatment.

Primary outcome measure is the proportion of patients with recurrence after 3 months. Secondary outcome measures are: 2) number of days not spent in hospital from initial treatment until 2 years afterwards; 3) major and minor morbidity; 4) disease specific and general quality of life; 5) anorectal function; 6) health care utilization and costs. A cost-effectiveness and cost-utility analysis of EMR against TEM for large rectal adenomas will be performed from a societal perspective with respectively the costs per recurrence free patient and the cost per quality adjusted life year as outcome measures.

Based on comparable recurrence rates for TEM and EMR of 3.3% and considering an upper-limit of 10% for EMR to be non-inferior (beta-error 0.2 and one-sided alpha-error 0.05), 89 patients are needed per group.

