### Outcome parameters

#### Primary outcome measure (for non-inferiority)

(1) Recurrence of neoplasia, defined as the presence of histologically proven neoplastic tissue in either visible recurrent lesions or in random biopsies, taken at surveillance endoscopies after the intervention strategy has been completed.

Any remnant adenoma identified and treated by EMR/APC at 3 months is considered part of the initial intervention strategy in both arms. Hereafter, patients will undergo surveillance endoscopies (with a GIF-Q160 endoscope) at 6, 12 and 24 months by an independent endoscopist who is blinded for the primary treatment. During each surveillance endoscopy recurrence will objectively be defined by the Higaki criteria for recurrence: tumor appearing within a clear resection scar; tumors with convergent folds; and tumors nearby a clear resection scar (within 5 mm)[49]. Targeted biopsies will be taken for histological confirmation; in case of an apparently healed normal scar without evidence of recurrence, 3 biopsies will be taken from the basis and 3 from the edges of the scar to detect occult recurrent neoplasia.

(2) Since equal recurrence rates for the TEM and EMR strategies are anticipated (equivalence trial), an additional outcome measure has been chosen that is responsive to both differences in initial care and to additional procedures that may be required in both strategies: the number of days that a patient is alive, outside the hospital and free of recurrence during two-year follow-up starting at the day of the initial treatment. Every patient therefore has potentially 730 days, and hospital days will be subtracted for initial treatment, readmissions, re-interventions and surveillance endoscopies. Adenoma recurrence or death will be considered as failure of the treatment strategy and no more additional days outside the hospital will be counted for such a patient.

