### Sample size calculation

Assuming a baseline recurrence rate of 3.3% for both TEM and EMR (average recurrence based on a systematic review) and considering an upper limit of 10% for EMR to be non-inferior, with a β-error of 0.2 and α-error of 0.05, 89 patients are needed per randomization group. As unexpected invasive cancers are expected in maximally 3% of patients, the total sample size will be 184 patients.

Since EMR is known to be effective in even more than 2 attempts, an upper limit of 10% seems reasonable, whereas higher recurrence rates would lead to many additional procedures which renders this strategy impracticable and probably not cost-effective.

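### The primary non-inferiority outcome is analysed with a chi-square test of equal rates, which never uses the 10% limit that sizes the trial

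*Protocol article*

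**What the plan says.** All references are to the protocol article.

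- **Outcome parameters.** Recurrence stands under the heading "Primary outcome measure (for non-inferiority". The same section later adds: "Since equal recurrence rates for the TEM and EMR strategies are anticipated (equivalence trial".
- **Sample size calculation.** "Assuming a baseline recurrence rate of 3.3% for both TEM and EMR", and "considering an upper limit of 10% for EMR to be non-inferior"; then "with a β-error of 0.2 and α-error of 0.05, 89 patients are needed per randomization group".
- **Abstract, Methods/design.** The same calculation, with the sidedness given: "beta-error 0.2 and one-sided alpha-error 0.05".
- **Data-analysis.** For the main outcome, "the Chi-square test will be used to compare the intervention groups (TEM versus EMR". The section explains why Kaplan-Meier methods are not used and makes intention-to-treat primary. For recurrence it gives no margin, confidence limit, significance level or decision rule.
- **Hypothesis and Economic evaluation.** The hypothesis is that recurrence rates are comparable. The economic evaluation becomes a cost-minimisation analysis if the two strategies prove clinically equivalent. Neither place gives a criterion.

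**The concern.** A non-inferiority conclusion requires rejecting the hypothesis that EMR is worse than TEM by at least the margin. A chi-square test addresses a different hypothesis, that the two rates are equal. If it is not significant, the data may still be compatible with an excess well beyond the margin. If it is significant, the result still does not say on which side of the margin the excess lies. The 10% limit appears only where the sample size is justified and never reaches the analysis.

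Two conclusions are at stake. The primary clinical question is left without a valid test. In addition, the switch to cost-minimisation, which removes recurrence as an effect from the economic evaluation that is the trial's main objective, depends on a finding of equivalence that the stated test cannot supply.

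**Working it through.** **Inputs.** Recurrence 3.3% in both arms, EMR limit 10%, beta 0.2, 89 per group (Sample size calculation); one-sided alpha 0.05 (Abstract); chi-square test (Data-analysis). Implied margin: 10% − 3.3% = 6.7 percentage points.

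**1. Which design gives 89?** The usual unpooled non-inferiority formula is

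n = (z₀.₉₅ + z₀.₈₀)² × 2p(1 − p) / margin²
= (1.645 + 0.842)² × 2 × 0.033 × 0.967 / 0.067² = 87.9, so 88 per group.

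That is one patient short of the stated 89. Alternatives are far off:

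| Design | n per group |
|---|---|
| Non-inferiority, 6.7 points, one-sided 0.05 | 88 |
| Non-inferiority, 6.7 points, one-sided 0.025 | 112 |
| Non-inferiority, 10 points, one-sided 0.05 | 40 |
| Test of difference, 3.3% v 10%, one-sided 0.05 | 170 |
| Test of difference, 3.3% v 10%, two-sided 0.05 | 216 |

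So the sample size fits a non-inferiority comparison on a 6.7-point margin and does not fit the test named in the analysis.

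**2. What does the chi-square test do when EMR is at the limit?** Exact binomial enumeration, 89 per arm, true rates TEM 3.3% and EMR 10%, Pearson test without continuity correction:

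- two-sided 0.05: non-significant with probability 0.572;
- one-sided 0.05: non-significant with probability 0.409.

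The Data-analysis section gives no level, so both are shown. If non-significance were read as comparable, these would be the chances of accepting an EMR strategy at the protocol's own limit. The planned chance is 0.05.

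**3. One possible result.** TEM 3/89 (3.4%), EMR 9/89 (10.1%). Two-sided chi-square p = 0.073, so no significant difference. The difference is 6.74 points and its one-sided 95% Wald upper limit is

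0.0674 + 1.645 × √(0.0337 × 0.9663/89 + 0.1011 × 0.8989/89) = 0.129,

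or 12.9 points, nearly twice the margin. Non-inferiority is not shown.

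**4. What would a confidence-limit rule do?** The rule is to conclude non-inferiority if the one-sided 95% upper limit for EMR minus TEM is below 6.7 points. Exact enumeration, 89 per arm:

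| Method | Power (3.3% v 3.3%) | One-sided error (10% v 3.3%) |
|---|---|---|
| Wald | 0.83 | 0.074 |
| Newcombe | 0.73 | 0.052 |
| Farrington-Manning score | 0.69 | 0.045 |

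**The case against.** **The article is condensed, and a confidence-limit rule may stand in the full protocol or analysis plan.** That would excuse silence. Here the article names a test for the main outcome and rules out an alternative, and the named test does not match the stated design. An analysis plan that followed this text would inherit the mismatch, and one that departed from it would contradict the article. The point stands.

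**Nothing says that a non-significant result will be read as non-inferior.** This is correct, and it limits the claim. A reader might infer that the trial plans to accept EMR on a non-significant p-value, with a 57% error rate. The documents do not support that as a stated rule. The 41% to 57% is what would follow if the gap were filled in that way.

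**Small expected counts.** About three recurrences per arm are expected, and a reader might infer that the chi-square approximation breaks down. It does not: at nominal two-sided 0.05 with 89 per arm, the exact size is 0.036 at 2%, 0.044 at 3.3%, 0.042 at 5% and 0.051 at 10% in both arms. The fault is the hypothesis tested, not the approximation.

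**Equivalence.** A reader might infer from this word that a two-sided equivalence design was intended and is underpowered. The outcome heading and the sample size are both for non-inferiority, and the remark about equivalence only explains why a second outcome was added. It is loose wording that should be made consistent.

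**Power.** A reader might infer from the 69% to 73% that the stated 80% is miscalculated. It is not: it follows a standard formula, and the Wald limit has 83% exact power. The lower figures come from choosing an interval that keeps the error near 5%.

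**The margin.** The 10% is given as an EMR rate, with a rationale on that scale. The 6.7 points is inferred from the sample size and is nowhere stated. Fixing the margin is for the sponsor.

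**Conclusion.** The analysis is wrong as written. The only test named for the primary non-inferiority outcome ignores the limit on which the trial is sized and cannot establish non-inferiority. That conclusion needs no assumption beyond the text.

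The size of the risk is conditional. With 89 per arm and true rates of 10% v 3.3%, reading non-significance as comparability would pass EMR in about 41% (one-sided 0.05) to 57% (two-sided 0.05) of trials, roughly eight to eleven times the planned 5%. This rests on an assumed test level and on a reading that the documents leave open but do not state. The sample size itself is not at fault.

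**What to change.** In the Data-analysis section:

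1. Replace the chi-square test as the primary analysis of recurrence with the one-sided 95% upper confidence limit (the upper limit of a two-sided 90% interval) for the EMR minus TEM recurrence rate, by a score or Newcombe method.
2. State the margin as a difference, and conclude non-inferiority only if the limit lies below it. A margin of 6.7 percentage points is the value that approximately reproduces 89 per group.
3. Keep the chi-square test at most as a secondary test of difference, with its level and sidedness stated.

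Elsewhere, use the same criterion for the switch to cost-minimisation in the Economic evaluation, and write non-inferiority consistently where the text now speaks of an equivalence trial.

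The change is to wording and needs no extra patients or data. Its cost is a less favourable power statement: at 3.3% in both arms, about 69% (score) to 73% (Newcombe), to be reported beside the formula-based 80%. A Wald limit would keep 83% power, but with a one-sided error of 7.4%.

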### Economic evaluation

#### General considerations

The economic evaluation of EMR against TEM for large rectal adenomas will be performed as a cost-effectiveness analysis as well as a cost-utility analysis from a societal perspective. The primary outcomes are the costs per recurrence free patient and the costs per quality adjusted life year respectively. The costs per patient free of complications as well as the costs per day alive and outside the hospital will be considered as secondary outcome. The time horizon is restricted to a follow-up of 24 months. Given this time span, discounting (of costs and effects) will be performed. Incremental cost-effectiveness ratios are calculated, reflecting the extra costs per additional recurrence free patient and the extra costs per additional QALY. Sensitivity analyses will be performed to account for sampling variability (following bias corrected and accelerated non-parametric bootstrapping), for plausible ranges in unit costs of surgery and endoscopic treatment, for (differential) discount rates of costs and effects, and for different health utility algorithms (see below). Subgroup analyses will be performed for patients with different rectal adenoma diameters (< 5 cm, 5–10 cm, > 10 cm) and distances of the adenoma from the anal verge (< 7.5 cm versus 7.5–15 cm) in order to tentatively assess differences in health care efficiency.

In case TEM and EMR turn out clinically equivalent, the study will be performed as a cost-minimization analysis[63].

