## Methods/Design

### Hypothesis

Transanal endoscopic microsurgery and extended EMR are both effective treatments for large rectal adenomas with comparable recurrence rates. However, EMR does not require general/spinal anesthesia or hospital admission and may be associated with lower morbidity. Therefore, EMR may improve quality of life and reduce health care costs.

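### An undefined finding of clinical equivalence would replace the cost-effectiveness and cost-utility analyses with cost-minimisation, and the recurrence result that the trial plans for would probably trigger it

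*Protocol article*

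**What the plan says.** The Objective section makes cost-effectiveness and cost-utility the main purpose of the trial. Under Economic evaluation, General considerations, the article names two primary economic results: "The primary outcomes are the costs per recurrence free patient and the costs per quality adjusted life year respectively". It then plans two incremental ratios, "reflecting the extra costs per additional recurrence free patient and the extra costs per additional QALY", and handles uncertainty as follows: "Sensitivity analyses will be performed to account for sampling variability (following bias corrected and accelerated non-parametric bootstrapping" (the parenthesis closes there).

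The section ends with a conditional rule: "In case TEM and EMR turn out clinically equivalent, the study will be performed as a cost-minimization analysis". The rule changes the form of the study. It does not add a cost-minimisation analysis beside the other two.

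Three other sections bear on it:

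- Outcome parameters introduces its second measure with the words "Since equal recurrence rates for the TEM and EMR strategies are anticipated (equivalence trial", and Sample size calculation assumes 3.3% recurrence in both arms with 10% as the upper limit for EMR.
- Data-analysis compares recurrence with a chi-square test.
- Hypothesis expects similar recurrence but adds that "EMR may improve quality of life and reduce health care costs".

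**The concern.** Cost-minimisation is sound when the effects of the two strategies can be taken as equal. The rule makes that assumption depend on a finding that the article does not define.

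If the finding is about recurrence, two things go wrong. First, neither a non-significant chi-square test nor one-sided non-inferiority shows that recurrence is equal. Second, recurrence does not stand in for QALYs. The Hypothesis section argues that quality of life may differ even though recurrence is comparable, and EQ-5D is collected at six time points so that QALYs can be derived.

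The result the trial is planned around would then remove the joint cost-and-QALY comparison from the main economic result. A QALY difference in either direction, its uncertainty and its correlation with cost would all be left out of the conclusion on value for money.

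**Working it through.** **Inputs.** Recurrence of 3.3% in both arms, a 10% upper limit for EMR, 80% power and 89 per group come from Sample size calculation. The one-sided alpha of 0.05 comes from the Abstract. The margin is 10 − 3.3 = 6.7 points.

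**The plan's own figure.** n = (1.645 + 0.842)² × 2 × 0.033 × 0.967 / 0.067² = 87.9, so 88 per group against the stated 89. The total also agrees: 178 / 0.97 = 183.5, so 184. The design is therefore a one-sided non-inferiority comparison with a 6.7-point margin.

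**How often the switch would occur.** I enumerated all pairs of binomial counts with 89 per arm and TEM at 3.3%. Two candidate triggers were applied:

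- A: the Wald upper bound, d + 1.645 × SE, lies below 6.7 points.
- B: the uncorrected chi-square test is not significant at two-sided 0.05.

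| True EMR recurrence | A: non-inferiority shown | B: chi-square not significant |
|---|---|---|
| 3.3% | 0.83 | 0.96 |
| 8% | 0.19 | 0.75 |
| 10% | 0.07 | 0.57 |

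Under the planning assumption the switch is the likely outcome with either trigger. Trigger B would also select cost-minimisation in more than half of trials in which EMR truly sits at the limit of acceptability.

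**What the switch sets aside on QALYs.** The article gives no standard deviation for QALYs, so this part rests on assumptions. The 95% half-width of the QALY difference is 1.96 × SD × √(2/89). For an assumed SD of two-year QALYs of 0.1, 0.2, 0.3 or 0.4, it is about 0.03, 0.06, 0.09 or 0.12 QALYs. At an assumed €20,000 per QALY, that is about ±€590, ±€1,180, ±€1,760 or ±€2,350 per patient. Cost-minimisation treats this component as exactly zero.

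**Secondary check, recurrence ICER only.** Under the planning assumption the expected denominator is 0, with SE = √(2 × 0.033 × 0.967 / 89) = 0.0268, or 2.7 points. By the same enumeration, the observed difference is exactly zero with probability 0.17, so the ratio is undefined. It favours each arm with probability 0.41, and it is at most one patient with probability 0.48.

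This does not carry over to the QALY ICER, whose denominator is not planned to be zero.

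**How the two points interact.** With trigger A, an observed difference of zero almost always leads to the switch. With 7 recurrences in each arm, 1.645 × √(2 × 0.0787 × 0.9213 / 89) = 0.066, still below 0.067, whereas only 0.033 × 89 = 2.9 per arm are expected. Undefined ratios would therefore mostly be reported once the switch is removed, or if the trigger is something other than recurrence. Among the trials that trigger A leaves unswitched at 3.3% in both arms, about 86% still have a 95% Wald interval for the difference that includes zero. With trigger B, none of the unswitched trials do.

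**The case against.** The strongest reply is that the rule says clinically equivalent and does not mention recurrence. Elsewhere, in the Discussion, the article limits equivalence to efficacy when it means that. If the term also covers complications and quality of life, an EMR gain would itself block the switch and little would be lost. The rule is also pre-specified and carries a citation, whose content cannot be checked here. This stands in part: the recurrence reading is an inference, though Outcome parameters supports it by linking equivalence to equal recurrence. Pre-specifying a rule does not help if its condition is undefined. Even a broader condition would need a valid demonstration of equal QALYs, and the article sets none.

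Several stronger readings are tempting, but the article does not support them:

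- **That neither route answers the main objective.** The QALY ICER has no planned zero denominator, so the cost-utility analysis would be informative if it were carried out.
- **That all planned ratios rest on a zero denominator.** This applies to the recurrence ICER alone. Moreover, the ratios are the main result only when equivalence is not concluded, so an unconditional count of near-zero denominators mostly describes trials that would have switched.
- **That cost-minimisation would hide 6.7 extra recurrences per 100.** That is a limit, not a likely loss. With 3 TEM recurrences, 4 on EMR passes (1.1 + 1.645 × 2.9 = 5.9 points) and 5 fails (2.2 + 1.645 × 3.1 = 7.3 points). At a true 10%, non-inferiority is shown with probability only 0.07.
- **That QALY data would be discarded.** Patient outcome analysis derives QALYs without any condition, and Data-analysis compares quality-of-life scores. What is lost is the joint result with costs.
- **That the article omits cost-effectiveness planes or acceptability curves, or plans an invalid ICER interval.** A condensed article may leave display to the full protocol, and it does not say how the bootstrap results will be presented.

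**Conclusion.** The point holds in this form. A stated rule replaces the analyses named in the main objective on an undefined condition. On the natural reading, the planned result meets that condition with probability about 0.83 (non-inferiority) or 0.96 (non-significant chi-square). Neither finding justifies treating the effects as equal, and neither bears on QALYs. The main economic result would then rest on costs alone.

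The probabilities assume 89 analysed patients per arm, 3.3% recurrence on TEM, the two triggers described and a recurrence-based reading of equivalence. The QALY and euro ranges assume standard deviations and a threshold that the article does not give.

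The instability of the recurrence ICER is a real but secondary matter. It becomes more relevant once the switch is removed, so the fix has to deal with it.

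**What to change.** Delete the cost-minimisation sentence. State that the cost-effectiveness and cost-utility analyses will be carried out whatever the recurrence result, with cost and effect differences estimated jointly in the bootstrap already planned.

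Summarise both analyses as incremental net monetary benefit with intervals over a range of willingness-to-pay values. This keeps the QALY difference and its correlation with cost in the result, and it avoids dividing by a difference near zero. Give the recurrence ICER only as a point estimate, and only when its denominator is clearly non-zero.

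The cost is a change of wording and slightly more analysis work. No further patients or data are needed.
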